#### Randomization

We will embed randomization within the technology. Our statistician will generate a randomization table; the randomization sequence will be conducted in random blocks of different sizes (n=8 and n=12) to ensure balance among the groups and reduce predictability of the allocation process. Thus, randomization will occur automatically at the time of initial registration. Following randomization, there will be an allocation to receive the peer recruitment toolset or not to receive the toolset. Study staff will be blinded to allocation during initial baseline assessment and follow-up.

### Study Participants

Participants will be included if they are current smokers over 18 years of age and can read or speak English. Prisoners will be excluded. Pregnant women may be incidentally enrolled. In such cases, this research poses no risks to the fetus.

### Data Collection and Outcomes

S2S will include multiple data collection stages (Table 1). At each time point (1 week, 1 month, and 6 months), we will send participants email reminders to complete the online follow-up surveys. We will send up to four email reminders over the course of 2 weeks from the targeted follow-up date (eg, if the participant is due for their 6-month follow-up on January 1, we will send them reminders for the 2 weeks following that date). If participants fail to respond to our email messages, we will call them to complete the survey over the phone. To calculate the success of our intervention, we will use the RE-AIM framework and evaluate results along the RE-AIM dimensions for success of health behavior interventions including reach, effectiveness, adoption, implementation, and maintenance [30-32]. Table 1 provides a list of study outcomes associated with RE-AIM dimensions. Our primary and secondary outcomes are listed below.

**Table 1 table1:** Study measure by time points and associated RE-AIM dimensions.

Construct		Description	RE-AIM dimension
**Baseline measures**			
	Demographics	Age, gender, race, ethnicity, education level Contact Information	Reach
	Smoking habits	Current smoking habits	Reach
	Quit attempts	Readiness to quit Nicotine dependence Nicotine replacement therapy use E-cigarette use	Reach
	Family-based intervention and social network	Household status Smokers in social network Interest in family-based intervention	Reach
	Reach and registration	Number of users who saw and clicked on online advertisements Number of users who registered following online advertisements	Reach, Adoption
**1-month measures**			
	User feasibility and acceptability	User feedback on use of the system	
	Peer recruitment success	Number of peer recruiters Number of peers recruited	Reach, Adoption, Effectiveness
	Peer recruitment experience	Number of friend/family smokers a recruiter contacted for recruitment (network reached) Use of tools outside the Smoker-2-Smoker peer recruitment toolset Barriers/facilitators to peer recruitment Primary reasons a potential recruitee chose to be peer recruited or not	Reach, Implementation, Maintenance
	Perceived influence of peer recruitment on cessation	Beneficial to the participant’s quit smoking efforts Motivated to get support from those around the participant to quit smoking Increased the participant’s craving for cigarettes Made the participant feel like they were being helpful to their family and friends who are smokers	Effectiveness
**6-month measures**			
	7-day point prevalence smoking cessation	Do you currently smoke cigarettes (smoked even 1 puff in the last 7 days)? [33]	Effectiveness
	Biochemical verification of smoking cessation	NicAlert uses a dipstick to measure the level of cotinine in a sample of saliva. We will mail strips with instructions on how to take and return a picture of the results to us electronically.	Effectiveness
**Continuous measures**			
	Website engagement	Number of visits to decide2quit Number of pages used	Adoption
	Message feedback	Influence survey sent after each email (explicit)	Effectiveness

#### Effectiveness Outcomes

##### Smoking Cessation: 7-Day Point Prevalence and Verification by Saliva Test NicAlert

The primary outcome measure will be 7-day point prevalence at the 6-month follow-up. The 7-day point prevalence will be assessed by asking, “Do you currently smoke cigarettes (smoked even 1 puff in the last 7 days)?” [33] The 7-day window provides an appropriate stringent measure to account for a cross-sectional snapshot. In a cessation trial, biochemical verification is used to monitor for differential misclassification by the randomization group. The degree of misclassification is moderated by characteristics of the smoking cessation intervention [34]. Studies that are in-person and intense generally have more misclassification because of the personal connection between the smoker and the counselor and therefore require biochemical verification. Less misclassification occurs in low intensity, light-touch studies. Further, differential misclassification increases with intervention differences between two groups. Since our intervention and control are both texting interventions, the potential for differential misclassification is reduced. Further, requiring biochemical verification can, in fact, lead to additional issues, including refusal to participate, thus biasing the sample [34,35]. However, based on peer review, we are conducting biochemical verification. To reduce the potential for biasing the sample due to the need for biochemical verification, we are using an opt-in procedure to conduct biochemical verification among those who indicated they had quit smoking at 6 months. If a participant indicates they have quit smoking at 6 months, they are contacted by the research study staff to see if they would like to opt-in to the biochemical verification. If a participant opts in, they will be mailed the NicAlert test strips (Nymox Corporation, St Laurent, Quebec, Canada) within 24 hours with clear instructions on how to take a picture and return the picture of the results to us electronically. NicAlert is a semiquantitative method that uses a dipstick to measure the level of cotinine in a sample of saliva. The test strip displays the result in seven zones. Each zone represents a range of levels of cotinine/smoking (eg, zone 0: 0-10 ng/mL, a nonsmoker, zone 6: >1000 ng/mL, a heavy smoker). The results will be read as 0-6, and as recommended, any value ≥ 1 will be considered as tobacco use [36-38]. Our staff will also be available by phone to help the smokers complete testing. Participants sending back the sample will receive an additional US $50 incentive (as outlined in the consent form) for completing biochemical verification.

##### Risk Reduction (Reduction in the Number of Cigarettes Smoked)

We will calculate risk reduction by subtracting the number of cigarettes smoked at baseline from the number of cigarettes smoked at the 6-month follow-up.

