**Methods:**

The Smoker-to-Smoker (S2S) study is a 6-month hybrid effectiveness dissemination trial conducted nationally among English-speaking, current smokers aged ≥18 years. All eligible participants will register for the DISC (Decide2quit) and be randomized to the recommender system CTHC or the standard CTHC, followed by allocation to a peer recruitment toolset group or control group. Primary outcomes will be 7-day point prevalence and risk reduction at the 6-month follow-up. Secondary outcomes include recruitment rate, website engagement, and patient-reported outcomes collected via the 6-month follow-up questionnaire. All primary analyses will be conducted on an intent-to-treat basis.

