#### Hypothesis 3: Effectiveness

We assumed a control cessation rate of 15% [42], and a two-sided significance level of .05. A sample size of 300 in each group will achieve 80% power to detect a difference of 9% (quit rate in intervention=24%) in quit rates between the two groups, based on a Z-test with pooled variance. We will categorize the NicAlert test results into smokers and nonsmokers and use the chi-square statistic to test for differences. We calculated the detectable difference in risk reduction with 300 smokers in each group and a mean of 3.3 cigarettes in the comparison group, using SDs of 2 and 3 with 80% and 90% power, respectively. We will have 90% power to detect a difference of 0.80 (or smaller) in the number of cigarettes smoked between the two groups. This difference is likely to be achieved based on the results of our PCORI pilot, in which we achieved a reduction of 0.85 (4.15-3.3) in 30 days compared to smokers receiving the standard CTHC messages; smokers receiving the recommender CTHC had a higher reduction in the number of cigarettes at 30 days (Standard CTHC: mean 3.3; S2S adaptive CTHC: 4.15).

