To test Hypothesis 3 (effectiveness), we will compare participants randomized to enhanced CTHC and those randomized to standard CTHC. We will use the 7-day point prevalence cessation of the 6-month follow-up as the dependent variable in generalized linear models. Using mediation analysis, we will examine the potential mechanisms through which we anticipate the intervention to produce a beneficial effect. We will categorize the NicAlert test into smokers and nonsmokers’ categories and use the Chi-square statistic to test for differences. If risk reduction (decreased number of cigarettes smoked) is normally distributed, we will use the identity link function in the generalized linear model. We will also model risk reduction using count regression with a Poisson or negative binomial regression modeling if the variance of the distribution of risk reduction is over dispersed. For Hypotheses 2 and 3, we will compare African American smokers across the groups, and African American and white smokers for heterogeneity.

To assess the difference in smokers comparing the peer recruitment and standard recruitment, we will use a three-step strategy. First, we will collect data on covariates (minority status, education, readiness to quit, and income) that have been shown to differ between the peer recruitment and standard recruitment [26]. We will use these variables to adjust our overall models with the outcome of smoking cessation, comparing participants from peer recruitment and those from standard recruitment. Second, peer recruitment is, in many ways, analogous to clustering. Each person who is recruited by another individual is clustered in the group of the initial peer recruiter. Thus, some component of the difference is within the relationship between recruiter and recruitee. To address this issue, we included a marker for each “recruiter” as a fixed effect in the model. Third, we will use an advanced approach, termed complier-averaged causal effect analysis (CACE), to compare those who complied (peer recruited or not) in the intervention group with those who would have complied in the comparison group if they had been exposed to the intervention (peer recruitment). Thus, after adjustment using the first and second approach, we will conduct additional models using CACE.

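### Risk reduction is defined with its sign reversed and is also to be fitted by Poisson or negative binomial regression, which cannot take a signed change score; its primary status is stated inconsistently

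*Protocol article*

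**What the plan says.** **Definition.** Under Effectiveness Outcomes, the risk reduction subsection gives the only operational definition. The outcome is obtained by "subtracting the number of cigarettes smoked at baseline from the number of cigarettes smoked at the 6-month follow-up". The subsection's own heading describes a reduction in cigarettes.

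**Direction.** Hypothesis 3 in the study hypotheses textbox (Introduction) expects quit rates and risk reduction to be greater with the recommender system than with the standard one. The sample size text for Hypothesis 3 assumes "a mean of 3.3 cigarettes in the comparison group" and cites pilot reductions of 3.3 (standard) and 4.15 (recommender), both positive.

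**Models.** Statistical Analyses specifies an identity-link generalized linear model if risk reduction is normally distributed, and continues: "We will also model risk reduction using count regression with a Poisson or negative binomial regression modeling", with overdispersion as the stated condition. It names no dependent variable for the count model other than risk reduction. All tests are two-sided at .05.

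**Rank.** The Abstract says: "Primary outcomes will be 7-day point prevalence and risk reduction at the 6-month follow-up". The smoking cessation subsection says: "The primary outcome measure will be 7-day point prevalence at the 6-month follow-up". The list of secondary outcomes under Dissemination Outcomes does not name risk reduction.

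**The concern.** Three stated items do not fit together.

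1. The subtraction runs opposite to the direction that the hypothesis and the power calculation take for granted. Read literally, a greater value of risk reduction belongs to the arm that cut down less.
2. Poisson and negative binomial models describe non-negative counts. A change score is signed, whichever way it is subtracted. The count model is the only alternative named if the outcome is not normal, so it is the one relied on when the linear model's stated condition fails.
3. Whether risk reduction is a primary outcome depends on which section is read, so the article does not settle what would count as success on Hypothesis 3.

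At stake are the correct reading of the direction of effect and a usable fallback analysis for an outcome that the Abstract ranks as primary.

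**Working it through.** **Step 1: reproduce the plan's own figure.** Inputs from the Hypothesis 3 sample size text: 300 per group, SD 2 or 3, power 80% or 90%. From Statistical Analyses: two-sided alpha .05. The detectable difference is (z for alpha + z for power) × SD × √(2/n).

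- SD 3, 90% power: (1.960 + 1.282) × 3 × √(2/300) = 0.794. The plan says 0.80 or smaller, so this reproduces.
- Check: a difference of 0.80 at SD 3 and 90% power needs 296 per group, and 300 per group gives 90.4% power.
- SD 2: 0.457 at 80% power and 0.529 at 90% power.

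Multiplying every value by −1 changes neither the absolute difference in means nor the SD. Detectable difference, power and two-sided p-value are therefore the same under either sign.

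**Step 2: direction.** Let B be baseline cigarettes and F the 6-month count.

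| Participant | F − B (as written) | B − F (as the heading implies) |
|---|---|---|
| Quits (F = 0, B > 0) | −B, negative | B, positive |
| Cuts down | negative | positive |
| No change | 0 | 0 |
| Smokes more | positive | negative |

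Only B − F agrees with the heading, with Hypothesis 3 and with the positive figures 3.3 and 4.15.

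**Step 3: share of negative values.** The article gives no distribution, so a roughly normal shape is assumed, with the power section's means and SDs. The means are 30-day pilot figures. The share below 0 is Φ(−mean/SD) for B − F, and 1 minus that for F − B.

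| Mean | SD | Below 0, B − F | Below 0, F − B |
|---|---|---|---|
| 3.3 | 2 | Φ(−1.650) = 4.9% | 95.1% |
| 3.3 | 3 | Φ(−1.100) = 13.6% | 86.4% |
| 4.15 | 2 | Φ(−2.075) = 1.9% | 98.1% |
| 4.15 | 3 | Φ(−1.383) = 8.3% | 91.7% |

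Rounded to whole cigarettes, the B − F shares are about 1% to 10%.

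**Step 4: what the count models do with such data.** Both distributions assign probability zero to any value below 0, so one negative observation makes the likelihood zero. This was tried on one simulated data set (300 per arm, means 3.3 and 4.15, SD 3, whole numbers).

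- F − B: 85% of values were negative, and neither the Poisson nor the negative binomial fit gave usable estimates.
- B − F: 7% were negative. The software printed coefficients, but the log-likelihood was minus infinity, so they are not maximum likelihood estimates.

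Correcting the sign therefore does not make the count model valid.

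**The case against.** The strongest reply is that little of the inference is damaged, and much of that stands. The intended direction is plain from the heading, the hypothesis and the pilot figures. Tests are two-sided, so the sign changes no p-value and no power. The identity-link model is stated first, accepts signed values and needs no exclusions.

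A reader might infer more than the article supports:

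- **That the analysis of risk reduction cannot run, or breaches intent-to-treat.** The identity-link model can be fitted, and the article nowhere plans to drop or truncate participants with negative values. The defect is confined to the count model.
- **That a raw change score is an error because it is not adjusted for baseline.** Randomised groups can be compared on change without bias. Baseline adjustment gains precision by an amount that depends on a correlation the article does not report.
- **That two primary outcomes at .05 give a false-positive rate of 9.75%.** That figure, 1 − 0.95², needs independent tests and a rule that success on either outcome suffices. The article states no such rule. Quitters smoke no cigarettes, so the outcomes should be positively related and the rate lower. If both outcomes must succeed, there is no inflation.
- **That risk reduction must be secondary.** The sentence naming a single primary measure sits under the cessation subheading, Hypothesis 3 names both outcomes, and the secondary list omits risk reduction. Two primary outcomes is a coherent reading, and the choice is the sponsor's.

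What the reply does not remove is that the written formula contradicts the rest of the article and that the named count model is invalid for the variable it is applied to.

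**Conclusion.** The point holds in a limited form. The definition is reversed: a wording error that affects interpretation but not power or two-sided tests. Count regression of risk reduction is invalid under either sign. That conclusion needs only one participant with a negative value. The shares of 86% to 98% as written and 2% to 14% after correction also rest on an assumed normal shape and on pilot means at 30 days.

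The count model matters most if normality fails. That is plausible, because each quitter's change equals their whole baseline count.

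The Abstract and Methods conflict on the number of primary outcomes. The article does not allow the effect on error rates to be calculated, because it states no success rule. The analysis of 7-day point prevalence is untouched by the sign and count-model errors.

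**What to change.** 1. **Definition.** State risk reduction as baseline minus 6-month cigarettes, so that positive means fewer.
2. **Model.** Delete count regression of the change score. If a method for a non-normal outcome is needed, choose one of these:
   - Negative binomial regression of the 6-month count (quitters = 0) on arm and log baseline count. This estimates a rate ratio, whereas the sample size section powers an absolute difference, so it needs its own power statement.
   - Linear ANCOVA of the 6-month count on arm and baseline count with robust standard errors. This keeps the absolute scale in cigarettes. State that a lower count favours the recommender arm.
3. **Rank.** Make the Abstract and the Effectiveness Outcomes text agree. If both outcomes stay primary, say whether success needs both or either, and control the error rate if either suffices.

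**Cost.** The definition already requires both counts, so no new data are needed. The change is to wording, plus a power statement if the rate-ratio model is chosen. The Abstract reports preliminary analysis as underway, so the correction should be dated and documented before outcome results by arm are used.

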#### Dissemination Outcomes

Secondary outcomes include recruitment rate, website engagement, and patient-reported outcomes collected via the 6-month follow-up questionnaire.

#### Recruitment Rate

When smokers register on Decide2Quit, they will be assigned a unique identifier and their registration date and time will be recorded. We will compute recruitment time from these data as the time taken to recruit each participant from the time that the first participant in the group was recruited.

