In response to a Patient Centered Outcomes Research Institute (PCORI) call for communication and dissemination research, we proposed a dissemination study—Smoker-to-Smoker (S2S)—to test whether providing access to a peer recruitment toolset that facilitates recruitment of friends and family members to the intervention will increase recruitment rate and increase variability of the sample. Because of feedback from PCORI and peer review, we expanded our study to also test the effectiveness of a machine learning–based approach (recommender system) for computer-tailored health communication (CTHC). Thus, our project is a hybrid effectiveness dissemination trial including both effectiveness and dissemination hypotheses (Textbox 1). Conducting a hybrid study with both effectiveness and dissemination hypotheses raises some unique challenges in the design and analysis of our study. Our paper describes the intervention functions and the study protocol we developed to address previously mentioned challenges. We also describe the budget impact analysis we will use to assess the cost of implementing this intervention.

Study hypotheses.Hypothesis 1: DisseminationH1A: Peer recruitment will recruit a greater proportion of African American smokers compared to standard online recruitment.H1B: Peer recruitment will reduce recruitment time (time to recruit each participant) compared to standard online recruitment.Hypothesis 2: Repeated use of Decide2Quit functionsH2A: Repeated use among those exposed to the fully enhanced group (access to peer recruitment toolset and recommender CTHC) will be greater than repeated use among those exposed to (1) peer recruitment toolset only, (2) recommender CTHC with no peer recruitment toolset, and (3) standard group (no peer recruitment toolset and standard CTHC).H2B: Repeated use among those exposed to the peer recruitment toolset will be greater than repeated use among those exposed to the standard group.H2C: Repeated use among those exposed to the recommender CTHC will be greater than repeated use among those exposed to the standard group.Hypothesis 3: EffectivenessQuit rates and risk reduction among participants exposed to the recommender CTHC (A+B) will be greater than those among participants exposed to the standard group (C+D).

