**Figure 1 figure1:**
[figure not shown]
Flow of participant randomization. Allocation to receive the peer recruitment tools occurs in two phases or waves. Wave 1: Half of the enrolled smokers are randomized to receive peer recruitment tools, while the others do not receive the tools; and Wave 2: All subsequent smokers who are randomized to the effectiveness trial and also report they were peer-recruited are given access to the peer-recruitment tools.

The basic flow of a single hypothetical smoker through the peer-referral, registration, and subsequent initiation of new peer-recruitment is described in Figure 1. Peer recruitment will take place in waves. As is common in peer recruitment approaches, to initiate the waves, we will recruit the first wave (wave 0 or seeds) of smokers. Seeds will be recruited using online advertisements. Once a seed registers on Decide2Quit and receives the peer recruitment toolset, we expect the following to occur:

The seed consents to be in the study and recruit smokers from his/her network using the peer-recruitment tools (by sending a Facebook private message).The successfully peer-recruited smoker (wave 1 recruit) registers on the system and consents to recruit other smokers in his/her social network.The wave 1 recruit then continues the peer-recruitment chain, recruiting smokers his/her their social network.The successfully peer-recruited smoker then registers (wave 2 recruit). The waves progress until the target sample size is reached.

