### Sample Size

#### Hypothesis 1: Dissemination

Our previous work [26,27] showed that having access to peer recruitment increased the proportion of African Americans to 23%, compared to 11% in the initial seeds (those recruited by advertisements). Using 10% as the base rate in the nonpeer recruitment group (no access to peer recruitment), we estimated sample size requirements by varying the proportion in the peer recruitment from 16% to 20%. With these assumptions, for our primary aim, we will need 219 smokers in each group to detect a difference of 10% (power=80%, α=.05). If we reduce the difference to 8% and 6%, we will need 319 and 525 participants in each group, respectively. Given that we will work with our panel to encourage recruitment of African American smokers in the peer recruitment group and may see bigger differences than those in our pilot study, we will have adequate power, particularly with the proposed sample size of 600 in each recruitment method. For recruitment time, previous trials estimated that the mean number of days to recruit a sample of 700 smokers was 244 (SD 81) days [27,40]. Assuming that peer recruitment proceeds with the same rate and SD, we can detect a difference in recruitment time as low as 14 days. Since we expect the comparison rate to be much slower, we are adequately powered to detect differences with a sample of 600 (power=80%).

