### Statistical Analyses

All primary analyses will be conducted on an intent-to-treat basis. Secondary analyses will explore dose-response effects among those with variable levels of adherence to the intervention. All analyses will be two-sided, and the alpha error will be set at .05. We will begin our analysis by examining univariate statistics (means, medians, SDs, and 95% CIs) and distributions. We will examine the balance of participant characteristics by study groups and account for any imbalances in our multivariable analysis. As appropriate, differences in measured characteristics (ie, demographics and prebaseline smoking behaviors) by group will be tested using Chi-square tests of independence (categorical variables), analysis of variance (continuous variables), or the equivalent nonparametric tests, depending on the distribution of the variables. Differences in baseline characteristics of the intervention and comparison groups will be assessed.

To test Hypothesis 1, we will categorize the smokers as either African Americans or not, and then use the chi-square statistic to test for differences between the peer recruitment and standard groups. We will also compare mean recruitment time between the two types of recruitment method using a *t* test. We will explore possible factors that may not be balanced between the smokers recruited from the two methods. If we find any significant differences, we will develop a linear regression model to further adjust for the influence of the confounders on the time to recruitment outcome. Within the peer recruitment groups, we will conduct a secondary analysis examining differences in demographic characteristic between peer recruited and directly recruited smokers. Using data provided by search engine advertisement managers, we will evaluate the performance of our online advertisements (number of users registered on Decide2Quit following an advertisement on the search engine).

To test Hypothesis 2, we will use a generalized linear model, which includes indicators of peer recruitment and recommender CTHC and the interaction between the two indicators as independent variables.

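### The H1B recruitment-time outcome does not measure recruitment speed under the stated allocation, and it is biased toward making the toolset arm look slower

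*Protocol article*

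**What the plan says.** The Introduction's hypotheses box states H1B: "Peer recruitment will reduce recruitment time (time to recruit each participant) compared to standard online recruitment". Methods, Recruitment Rate, computes the outcome from registration dates and times, "as the time taken to recruit each participant from the time that the first participant in the group was recruited". Statistical Analyses will "compare mean recruitment time between the two types of recruitment method" with a t test, two-sided at .05.

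Study Design and the Figure 1 caption fix who is in which group. Direct recruits are randomised, half to the toolset and half to no toolset. For peer recruits the caption says: "All subsequent smokers who are randomized to the effectiveness trial and also report they were peer-recruited are given access to the peer-recruitment tools". The waves continue until the target sample size is reached.

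Sample Size, Hypothesis 1, gives a mean of 244 days (SD 81) from previous trials, plans 600 per recruitment method, and concludes that "we can detect a difference in recruitment time as low as 14 days". The Abstract and the Dissemination Outcomes section list recruitment rate as a secondary outcome.

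**The concern.** The section is headed as a rate but defines neither a count per unit of time nor a time to reach a fixed number. It gives each person a position in the accrual window, and the analysis averages those positions. Two groups that accrue evenly over the same window have the same average position, however many people each enrols.

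The allocation adds a direction. Both arms' direct recruits come from one stream. The only difference between the arms is the peer recruits, and each of them registers later than the person who recruited them. The better peer recruitment works, the more late dates the toolset arm collects. H1B is one of two dissemination hypotheses in a hybrid trial. Read as planned, effective peer recruitment could be reported as no faster, or as slower.

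**Working it through.** **Inputs.** Outcome, test and allocation are as set out above. The figures 244, 81, 14 and 600 come from Sample Size, Hypothesis 1. The number of peers each toolset holder brings in (R), the lag from recruiter to recruit (mean L days) and the rate of direct registration are assumptions, so ranges are shown.

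**1. The plan's own figure.** Detectable difference = (1.96 + 0.84) × 81 × √(2/n). With n = 600 per group this is 13.1 days; with n = 525 it is 14.0. The stated 14 days is slightly conservative at 600 per group and is not an arithmetic error.

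**2. What the mean responds to.** With even accrual over T days, the mean registration day is T/2. Take T = 365 and 300 registrants: the first registers on average at 365/301 = 1.2 days, so the measured mean is 182.5 − 1.2 = 181.3. With 600 registrants it is 182.5 − 365/601 = 181.9. Doubling the rate from 0.82 to 1.64 per day leaves the mean practically unchanged.

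**3. Direction.** Suppose toolset seeds register at a constant λ per day and each brings in R peers after a lag with distribution function F. First-generation peers then register on day t at rate λ·R·F(t). F never falls, so peer registrations are weighted to the later part of the window and their mean lies above T/2. Later generations repeat the argument. The toolset mean is therefore pushed up, not down.

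**4. Size with a fixed 365-day window.** 600 direct recruits split 1:1, L = 30, 200 runs per row, toolset v no toolset:

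| R | Enrolled | Mean days | Significant, wrong direction | Significant, right direction |
|---|---|---|---|---|
| 0 | 300 v 300 | 181.4 v 180.8 | 3.0% | 4.5% |
| 0.3 | 413 v 300 | 186.0 v 181.5 | 9.0% | 2.5% |
| 0.6 | 657 v 300 | 196.3 v 181.3 | 52.5% | 0% |

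At R = 0.6 the toolset arm recruits 657/365 = 1.80 per day against 300/365 = 0.82, a ratio of 2.19. Its mean recruitment time is nevertheless 15 days longer.

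**5. Size when accrual stops at 1200.** Two direct registrations per day assumed, mean lags from 3 to 30 days:

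| R | Significant, wrong direction |
|---|---|
| 0.25 | about 5-11% |
| 0.5 | 11-42% |
| 0.75 | 28%, 48%, 69%, 93% at lags of 3, 7, 14, 30 days |

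Right-direction significance is 0-8% throughout. A repeat run gave closely similar figures; at the lowest yield and shortest lag the two means are practically equal.

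The only pointer to R is the pilot in the section on the peer recruitment toolset, where 190 smokers recruited 569 more. That is 569/(190 + 569) = 0.75 per person if recruits could recruit in turn, which is an assumption.

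**6. The reading under which the measure works.** If each group fills 600 on its own clock at a constant rate, filling in 200 v 244 days gives means of 100 v 122, which is the correct order. Under the stated allocation, though, D direct and P peer recruits with D + P = 1200 give a toolset arm of D/2 + P = 600 + P/2 and a no-toolset arm of 600 − P/2. These are equal only if P = 0.

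Chain growth can upset the order even on separate clocks. With N(t) = n₀·exp(rt) reaching 600 in 200 days, the mean is 200 − (600 − n₀)/(600r), where r = ln(600/n₀)/200. This is 152 from 10 seeds, 126 from 50 and 81 from 190, against 122 for a steady group that takes 244 days.

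**The case against.** The strongest defence is that the planners had two separate recruitment streams in mind, each filling 600 from its own first registrant. The sample-size section suggests this, and step 6 shows that the mean then ranks constant rates correctly. That stands as a reading of the sample-size section, but it cannot be squared with Study Design and the Figure 1 caption, which split one direct stream and add every peer recruit to one arm.

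The wording about types of recruitment method could also mean peer-recruited against directly recruited people. The sign could then go either way (at R = 0.3, L = 14, the means were 180.4 v 181.3 days), and the measure would still not be a rate.

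Second, the reversal depends on lag. Recruitment is by private Facebook message, so short lags are plausible, and at a 3-day lag even R = 0.75 gives 28%, not 93%. This is right, and it limits the claim. A reader might infer that the planned test will reverse the dissemination conclusion; the protocol gives no lag and no expected yield from which to say so.

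Three further inferences are not supported:

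- **The SD of 81 is misapplied.** It can equally be read as a participant-level SD across 700 people, and the cited sources are not at hand.
- **The 14-day figure is wrong.** Step 1 shows that it is not.
- **The fallback regression adjusts for race.** It is conditional and names no covariates. Minority status is listed only for the cessation models.

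**Conclusion.** The outcome is wrong as written for H1B. Under the stated allocation, mean days since the group's first registration does not measure recruitment rate, so it cannot support the hypothesis, and it is biased toward making the toolset arm look slower. The insensitivity to rate follows from concurrent even accrual alone. The direction also needs roughly constant direct accrual; a large late burst of direct recruits could change the sign. The size rests on assumed yield and lag: from hardly visible at 0.25 recruits per holder to wrong-direction significance in 28-93% of runs at 0.75. Certain reversal should not be claimed. The defect is confined to a secondary dissemination outcome and does not touch cessation or risk reduction.

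**What to change.** Define the H1B outcome as registrations per calendar day in each arm, from the first registration in the study to the close of enrolment. Report the rate ratio, toolset to no toolset, with a confidence interval from resampling or clustering on the directly recruited seed, so that each chain stays together. Keep the present measure as descriptive only. Bring the H1B wording, Recruitment Rate, Sample Size and Statistical Analyses into line, including which groups are compared. Restate the detectable difference for the rate ratio, since 14 days applies to the present outcome.

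State how peer recruits are credited. Because the allocation places all of them in the toolset arm, the ratio can hardly fall below 1 unless referrals made by no-toolset participants are credited to their recruiter's arm. Counting descendants per seed in a fixed window is a possible supplement, but it has a different numerator, unit and censoring and is not interchangeable with the rate.

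Cost: registration dates and times are already recorded and a recruiter marker is planned, though the protocol does not say that the marker covers referrals made outside the toolset. The main cost is timing. The Abstract reports enrolment complete and preliminary analysis under way, so the change must be labelled either as made before the H1B analysis or as post hoc.
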